### 2.5. Recruitment

Participants will be prospectively included and compared with historical controls from the same sites. Participants meeting all the inclusion and not any of the exclusion criteria will be offered to start on the HR^35^ZE arm. After 8 weeks, participants will be managed according to the national TB guidelines.

The selected retrospective participants will provide a comparison for the primary safety outcome, and to the secondary efficacy outcome of culture conversion at 8 weeks using MGIT media. 

We adhered to all Pockock’s principles for historical controls except for the use of information from participants that were previously randomized in clinical trials [23]. To avoid the selection bias that may arise because of this limitation, we aim to include all adult patients fulfilling the inclusion criteria treated with HR^10^ZE in the participating sites between January 2017 and December 2019 (to avoid the influence of the 2020–2021 SARS-CoV-2 pandemic in TB diagnoses and follow-up). Thus, the records of all patients from that period with pulmonary and extrapulmonary rifampicin susceptible tuberculosis will be reviewed. We will capture the severe or grade 3 adverse events and week 8 microbiological status from those who are ≥60 years, or ≥18 years and have a diagnosis of diabetes, malnutrition, HIV, HBV or HCV coinfection, other stable chronic liver diseases, or TB meningitis, and have no pharmacological immunosuppression. We intend to control the retrospective cohort to match the prospective one for age, sex, cavitation in lung TB, and severity in TB meningitis. In case not enough matched controls are not found, we will extend the search with patients until the calculated sample size in the control arm is achieved. The historical cohort will include participants from only Spain, Portugal, and Paraguay and not likely from the Netherlands, as optimized doses of rifampicin have been used in both Dutch sites for more than a decade in the same participant subgroups as included in our study.

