### 2.8. Assessment of Study Outcomes, Analysis Groups, and Duration of Follow-Up

The primary safety hypothesis is that the incidence of adverse events in the high dose rifampicin (35 mg/kg) supplemented with isoniazid, pyrazinamide, and ethambutol [HR^35^ZE] during the first 8 weeks of treatment will not exceed that of controls on a standard HRZE regimen (rifampicin 10 mg/kg) [HR^10^ZE]. The HR^35^ZE regimen will be considered unsafe if in a non-inferiority analysis, the upper limit of the 95% confidence interval of the difference of proportions in grade ≥ 3 AE (according to CTCAE scale version 5) between the experimental and the historical control arm exceeds 8%. The most common adverse events related to therapy with higher rifampicin doses were vomiting, headache, hyperuricemia, pain in the extremities, and pruritus. No significant differences according to rifampicin dose (from 10 to 35 mg/kg) were found in a recent systematic review and in a retrospective study collecting the real-life experience from a Dutch center [24,25].

To assess the AE and ensure a homogeneous evaluation of their grade, severity, expectedness, and treatment relatedness, we will administer a standardized training for the investigators from all different sites. In addition, both for the prospective and the retrospective cohorts, grade 3 or higher adverse events and SAE will be reviewed by the trial’s Steering Committee for relatedness classification. When no consensus is reached, the Data and Safety Monitoring Board formed by experts independent from the trial will make the final decision.

Tolerability will be measured as any adverse event (grade 1 to 4), treatment dropout rate, and any dose reduction. For efficacy outcome, the hypothesis is that in DS-TB participants (pulmonary disease), the proportion of participants experiencing successful treatment outcomes (culture and smear negative) at the end of the intensive phase of treatment on HR^35^ZE will be non-inferior to that of controls on HR^10^ZE. The HR^35^ZE regimen will be considered ineffective if the lower limit of the 95% CI of the proportion of participants with a negative sputum culture (sputum sterilization), or unable to produce sputum if they have a previous negative culture at week 8, is more than 10% lower than that of historical controls treated with HR^10^ZE. Other exploratory outcomes will be reported descriptively. 

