### 2.10. Main Outcomes Analysis

The primary safety outcome will be analyzed as the proportion of participants in the HR^35^ZE and historical HR^10^ZE groups that received at least one dose of treatment with an unfavorable outcome after 8 weeks of experimental treatment start. According to the clinical and laboratory information, participants will be classified as having an unfavorable outcome if they suffered one or more grade ≥ 3 AE or SAE that are possibly, probably, or definitely related to rifampicin OR they did not complete their treatment because of other reasons OR were lost-to follow-up. High doses of rifampicin will be considered non-inferior to standard doses if the upper boundary of the 95% CI of the proportion of participants with an unfavorable outcome is less than 8% that of the point estimate in the historical standard dose group.

Efficacy will be assessed as the proportion of participants with pulmonary TB in the HR^35^ZE and the historical HR^10^ZE groups that have sputum culture conversion in liquid media at week 8. The unfavorable efficacy outcome will be defined as having a positive sputum culture at week 8.

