#### 2.11.1. Microbiological Evaluation

We will collect sputum samples from the experimental treatment pulmonary TB participants at week 1, 2, 4, 6, and 8, and compare the baseline bacterial load with the bacterial load at each of these time points as estimated by the time to positivity in days, as compared to that at baseline [9]. Time to positivity (TTP) is a good correlate of bacterial load and this information is readily available from the MGIT system. In addition, we should be able to estimate CFU count using a formula previously published [26]. In addition, we will compare the changes in TTP with a baseline and follow-up breath signal of the AeoNose™ device, an electronic nose that analyzes volatile organic compounds (VOC) in exhaled air. Pilot studies show that the VOC signal decreases during treatment; hence, it has potential as a biomarker to estimate bacterial load [27].

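### The stated matching factors and control data capture include no direct measure of pre-treatment bacterial load, so the week-8 culture comparison is open to confounding by load

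*Protocol article*

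**What the plan says.** All references are to the protocol article.

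- **Endpoint (2.10).** "Efficacy will be assessed as the proportion of participants with pulmonary TB" with week-8 conversion in liquid media, in the HR35ZE and historical HR10ZE groups. "The unfavorable efficacy outcome will be defined as having a positive sputum culture at week 8".
- **Decision rule (2.8).** The regimen is called ineffective if the lower 95% confidence limit for culture negativity "is more than 10% lower than that of historical controls treated with" the standard dose.
- **Control of confounding (2.5).** The retrospective cohort is to "match the prospective one for age, sex, cavitation in lung TB, and severity in TB meningitis". If matches run short, "we will extend the search with patients until the calculated sample size in the control arm is achieved".
- **Data taken from controls (2.5).** Two items are named: severe or grade 3 adverse events, and the microbiological result at week 8. Controls serve "the secondary efficacy outcome of culture conversion at 8 weeks using MGIT media".
- **Bacterial load (2.11.1).** "Time to positivity (TTP) is a good correlate of bacterial load and this information is readily available from the MGIT system". The planned use is serial change from baseline in the experimental pulmonary participants.
- **Availability (2.11).** The section opens by warning that its data will be lacking for most historical controls.

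**The concern.** A patient who starts with a heavier sputum load is more likely to be culture-positive at week 8 on either dose. Load is thus a strong prognostic factor for exactly this endpoint, and without randomisation nothing balances it by design.

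Of the four matching factors, TB-meningitis severity has no bearing on a pulmonary culture endpoint, age and sex are indirect, and cavitation is a partial proxy. Even the balance on cavitation is not assured once the control search is widened.

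Imbalance is plausible on the document's own account. Controls date from 2017 to 2019 and recruitment starts in late 2022 or early 2023 (section 5). Section 2.5 itself cites pandemic effects on TB diagnosis. The Dutch sites recruit but are unlikely to supply controls. Prospective participants must also consent and pass exclusions that include investigator judgement (2.4). None of this fixes the direction.

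The timing matters. An analysis plan can add a covariate later, but not one that was never extracted from the control records.

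**Working it through.** The document gives no expected conversion rate, no efficacy sample size and no load distribution, so there is no stated figure to reproduce. What follows is an illustration on assumed inputs.

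**Inputs**
- Margin: 10 percentage points (section 2.8, reading its 10% as an absolute difference).
- Conversion: 70% with high and 90% with low pre-treatment load (assumed).
- Imbalance in the share with high load: 10, 25 or 40 points, centred on 50% (assumed).
- Evaluable per arm: 134 × 0.95 ≈ 127 from section 2.9. This is an upper figure, because efficacy is restricted to pulmonary TB. 80 per arm is an assumed lower case.
- No allowance for cavitation matching, which could reduce the imbalance.

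**Step 1: shift in the crude difference**

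Shift = imbalance × (0.90 − 0.70)
- 0.10 × 0.20 = 2 points
- 0.25 × 0.20 = 5 points, half the margin
- 0.40 × 0.20 = 8 points

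**Step 2: effect on the decision, normal approximation**

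P(declare non-inferiority) = Φ((d + 0.10)/SE − 1.96), where d is the expected crude difference and SE = √[(p_E(1−p_E) + p_C(1−p_C))/n].

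*Fewer high-load patients on HR35ZE, true effect exactly −10 points (nominal error 2.5%).* Worked case, imbalance 25 points, n = 127:
- p_C = 0.625 × 0.70 + 0.375 × 0.90 = 0.775
- p_E = 0.375 × 0.60 + 0.625 × 0.80 = 0.725
- d = −0.05; SE = √[(0.1994 + 0.1744)/127] = 0.0542
- Φ(0.05/0.0542 − 1.96) ≈ 15%

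*More high-load patients on HR35ZE, no true difference.* Worked case, imbalance 25 points, n = 127:
- p_C = 0.825, p_E = 0.775, d = −0.05, SE = 0.0501
- Φ(0.05/0.0501 − 1.96) ≈ 17%

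| Imbalance | Shift | False non-inferiority, n = 80 / 127 | Power when truly equal, n = 80 / 127 |
|---|---|---|---|
| 0 | 0 | 2.5% / 2.5% | 35% / 51% |
| 10 points | 2 | 5% / 6% | 24% / 36% |
| 25 points | 5 | 11% / 15% | 12% / 17% |
| 40 points | 8 | 21% / 31% | 5% / 6% |

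**Step 3: sensitivity to the assumed gradient**

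With conversion 90% at low load and 75%, 65% or 55% at high load, and imbalances of 10 to 30 points, the shift runs from 0.10 × 15 = 1.5 to 0.30 × 35 = 10.5 points. False non-inferiority then runs from 4% to 29% at 80 per arm and from 5% to 43% at 127 per arm.

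**The case against.** **The adjustment may sit in the analysis plan.** Section 2.10 defines an endpoint and two groups; it does not say that the analysis is crude. A model's covariates are commonly left to an analysis plan, and this article condenses a fuller protocol. That stands: the absence of an adjusted model here is not a defect. What the article does state is the matching list and the items captured from controls, and load is in neither.

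**The data may not exist.** A reader might infer from "Time to positivity (TTP) is a good correlate of bacterial load and this information is readily available from the MGIT system" that time to positivity lies ready for both cohorts and was simply overlooked. The document does not support that. The sentence describes the MGIT system in a paragraph on experimental participants; section 2.11 warns that its data will be missing for most controls; and section 2.5 mentions MGIT only for the week-8 result, so a common laboratory system for the diagnostic culture is not stated. This limits what can be promised, but does not end the matter. A diagnostic smear or culture is a different item from the serial research measurements of section 2.11. Conversion presupposes an initial positive result, and the microbiological populations in Table 2 require culture confirmation. An attempt at retrieval is reasonable.

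**The bias is already conceded.** Section 2.15 admits that the design is prone to bias and that the results should inform future trials, and efficacy is secondary. True, but section 2.8 still attaches a formal verdict to the comparison, and a general caveat does not replace collecting a prognostic variable.

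**The size is assumed.** It is. Cavitation matching could make it smaller.

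**Conclusion.** The point holds in a limited form: the stated matching and control-capture lists omit any direct measure of pre-treatment load, so the week-8 comparison can be confounded by it in either direction. The actual size cannot be known from the document. On the assumed 70% versus 90% gradient, imbalances of 10 to 40 points move the difference by 2 to 8 points against a 10-point margin, before any effect of cavitation matching. No observed imbalance is reported.

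Two stronger readings should be resisted. The document does not show that load data are on record for most controls. Nor does adjustment promise a narrower interval: in a non-randomised comparison, adjusting for an unbalanced covariate can widen it. The gain to claim is less bias.

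This should be settled before control records are extracted, as a recommended change to a secondary endpoint rather than a flaw in the primary safety analysis.

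**What to change.** 1. Add pre-treatment sputum smear grade, and MGIT time to positivity where on record, to the control record form.
2. For HR35ZE participants, take the same measure from the last sputum before the first anti-TB dose. Section 2.6 allows screening tests after treatment has begun, so the trial baseline sample may not be pre-treatment.
3. Use one common measure in both cohorts: smear grade, or time to positivity if sufficiently complete. Do not mix the two scales in one covariate.
4. Report a week-8 risk difference adjusted for that measure, cavitation, age and sex, with its 95% CI against the 10-point margin, beside the unadjusted difference and with missingness by cohort. For example, standardise from a logistic model.
5. If the measure is largely missing in controls, make the adjusted estimate a sensitivity analysis and state residual confounding by load as a limit on the efficacy conclusion.

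**Cost:** one or two laboratory fields per pulmonary control, retrieval of the pre-treatment result for participants already on treatment at screening, and one model. The main downside is incomplete control records, possibly to an unequal degree across sites; how incomplete cannot be judged from the document.

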### 2.11. Secondary Objectives

Secondary objectives can be grouped into 4 categories. The analyses will be descriptive as these data will not be available from most of the historical HR^10^ZE controls.

#### 2.11.1. Microbiological Evaluation

We will collect sputum samples from the experimental treatment pulmonary TB participants at week 1, 2, 4, 6, and 8, and compare the baseline bacterial load with the bacterial load at each of these time points as estimated by the time to positivity in days, as compared to that at baseline [9]. Time to positivity (TTP) is a good correlate of bacterial load and this information is readily available from the MGIT system. In addition, we should be able to estimate CFU count using a formula previously published [26]. In addition, we will compare the changes in TTP with a baseline and follow-up breath signal of the AeoNose™ device, an electronic nose that analyzes volatile organic compounds (VOC) in exhaled air. Pilot studies show that the VOC signal decreases during treatment; hence, it has potential as a biomarker to estimate bacterial load [27].

#### 2.11.2. Pharmacokinetics

Drug exposure is a better predictor of treatment success than the total dose. There is extensive pharmacokinetic data on rifampicin at doses up to 50 mg/kg/day, but the target population in RIAlta was not represented. To capture rifampicin exposure in steady state, we will collect PK samples at week 4 after experimental treatment starts following a simplified sampling strategy (2, 4, and 6 h) to predict exposure (AUC0-24) [28].

#### 2.11.3. Pharmacogenetics

The genes involved in rifampicin metabolism and hepatotoxicity, whose expression is modified by rifampicin itself, are thought to explain the wide inter-individual variations observed in rifampicin exposure and development of toxicities among certain individuals. The RIF gene is mutated at three sites: CYP2C9*2, CYP2C9*13, and CYP2C19*2, which might have significance in drug-induced liver injury. The study by Su et al. found that the CYP2C9*2 genotype was significantly associated with drug-induced liver injury [29]. In Europeans and admixed Americans, CYP3A4*22 is the most common allele (minor allele frequency, MAF 5% and 2.6%, respectively) with *3 and *2 contributing to the genetic variability in the former study. In contrast, CYP3A4*15 (MAF 2.5%) and CYP3A4*18 (MAF 1.9%) constitute the only common CYP3A4 alleles in Africans and East Asians [30]. A subset of participants will be offered to participate in a genetic analysis searching for variants in the genes *SLCO1B1*, *ABCB1*, *UGT1A,* or *PXR*. We will correlate these results with the exposure obtained from the PK sub-study as well as with the clinical and microbiological outcomes [31]. 

#### 2.11.4. Health Economics and Quality of Life

We will assess the costs (direct and indirect), the incidence of catastrophic costs (those that are ≥20% of the household’s annual income), and the changes in quality of life associated with the use of high dose rifampicin in this trial population. The EUSAT-RCS consortium has developed a survey tool to capture the costs for TB patients and their caregivers based on that described by the WHO [32,33].

### 2.12. Ethical Approvals

The trial protocol has been registered in EudraCT and Clinicaltrials (EudraCT 2020-003146-36, NCT04768231 respectively), and has already been approved by the Medical Ethics Committees from Vall d’Hebrón Hospital in Barcelona, Spain, and Radboudumc in Nijmegen for The Netherlands (approval number: NL75346.091.20). Additional ethics approval will be acquired by each participant country. 

### 2.13. Sharing of Trial Findings

Trial results regarding its main safety and efficacy outcomes, and all secondary outcomes will be summarized in the final trial report and submitted to regulatory authorities and ethics committees as required in each participating country. In addition, the results will be made public through peer-reviewed journals, and the generated datasets will be made available according to the European Commission requirements and data protection regulations.

### 2.14. Participant and Public Engagement

No structured community engagement was followed during the design of this trial. We will engage with participants, TB patient associations, and the community to discuss the results of this study and contextualize them and ensure a relevant impact. Furthermore, these results will inform the design of future projects, in which a continuous dialogue with the TB research community will be of utmost importance.

### 2.15. Strengths and Weaknesses of the Design

The population included in the RIAlta trial includes people from groups typically excluded from clinical trials, and will thus outline the applicability of optimized doses of rifampicin, with exploratory data on late clinical efficacy endpoints (relapse-free survival). The simultaneous collection of pharmacokinetic, microbiologic, and a breath signature will help provide a complete perspective on the intervention.

However, the non-randomized design and the use of historical controls make the RIAlta trial especially prone to bias. Although preventive measures have been taken, the results should be considered as informative to future trial designs rather than general practice changing.

## 3. Discussion

RIAlta is a multinational, open label, non-randomized phase 2b/c trial that aims to bridge an important knowledge gap on the safety of optimized rifampicin doses in vulnerable TB patients that are more prone to suboptimal treatment outcomes and drug toxicities because of age and comorbidities. The trial will provide useful information on the efficacy and pharmacokinetics of 35 mg/kg rifampicin dosing and explore possible correlations between occurring adverse events and the rifampicin genetic polymorphisms involved in metabolism and hepatotoxicity. It will evaluate the usefulness of exhaled VOCs as biomarkers of early treatment response. Finally, the study will evaluate the social and economic circumstances of the participants.

There are no validated surrogates for early treatment response for extra-pulmonary TB. Efficacy studies at 8 weeks based on sputum culture conversion does not include this patient population. The cure at the end of treatment is also difficult to confirm in this group because of the need of invasive samples that are not indicated as the procedure might pose extra/unnecessary risks to patients’ lives. As a result, most of the trials exclude persons with extrapulmonary TB and the safety and efficacy information are extrapolated from pulmonary TB studies. It is well known that the pharmacokinetics of antimicrobials may vary according to the site of infection [13]. To address this, our study will obtain information about pulmonary and extrapulmonary TB in parallel. The correlation between intermediate data about sputum culture conversion and change in sputum bacterial load as estimated by the TTP for pulmonary TB participants and change in VOC in all participants will enable us to explore if the breath signature changes could be used as surrogate markers for extra-pulmonary TB. This could open the path for non-invasive biomarker validation and future inclusion of people with extrapulmonary TB in regulatory trials.

Therefore, the population included in this study belong to the other risk factors groups for failure and relapse that have been under-represented in previous clinical trials [4,22]. As a phase 2 study, the main aim of this clinical trial is to evaluate safety of rifampicin defined as the rate of participants suffering grade 3 or higher adverse events or severely adverse events. This information will be likely available from historical controls although it was not systematically collected. Grade 1–2 adverse events, which are considered tolerability problems, are not typically reported in clinical records, or the information about them is not complete, thus making it difficult to make comparisons. To address this, we have developed adverse events monitoring and management guidelines, which will be harmonized at all centers for the prospective part. Extensive training will be provided to the investigators at each site. 

It is important to acknowledge the main limitations related to this trial design. Because of the limited recruitment capacity within our consortium and budgetary constraints, we decided to use historical controls (rifampicin 10 mg/kg along with the same TB regimen) and assign all prospectively recruited participants to the 35 mg/kg dose. This results in a non-randomized design as all participants will be assigned to the experimental arm and compared with historical controls. Hence, another limitation is that information about tolerability is often incomplete or not reported in clinical records, and the endpoints in the different sub-studies are not performed in daily clinical practice. For similar reasons, the sample size is too small for a formal subgroup analysis. The results will inform a larger phase 3 trial with power calculations for relevant subgroups.

Having one PK sampling at week 4 will allow us to show the percentage of participants reaching the target exposure (AUC/MIC) when in a steady state after rifampicin induction of its own metabolism. In contrast, this approach will not provide information about exposure during the first week of treatment, when most of the bacterial killing occurs. Nevertheless, this knowledge will aid our understanding if optimized rifampicin dosing is more likely to meet target rifampicin exposure. 

Any attempt to improve TB treatment outcomes must also consider its impact on the socio-economic background of the people who suffer because of TB. This includes patients with active TB infection and extends to their families and communities. A treatment that is safe and effective, but not well tolerated or takes longer to treat has consequences not only on individuals and families but also on a society. For example, frail TB patients might be absent from the workforce for a longer time, threatening financial security of the whole family in informal economies. Furthermore, caregiving activities of a family member might be over-stretched to meet the needs of patients that affects both direct and indirect costs of TB. Hence, the global impact of a new treatment scaled to a programmatic level could be unforeseen inconveniences for the patients and their families beyond the biological aspects of health. 

In the past few decades, very few clinical trials on TB have been conducted in the European region because of low TB incidence (and hence low recruitment speed) and increased costs as compared to other regions. For those conducted, none of the trials have focused on the use of an optimized rifampicin dose in the targeted patient population [34]. European sites are still important for external validation and, importantly, to offer innovative treatment opportunities for people with TB. In addition, whereas implementing clinical trials in low-and middle-income countries has specific logistic challenges, working closely in both realities through collaborative consortiums such as ours, EUSAT-RCS, creates a unique milieu for capacity building. Via mutual exchange of personnel and expertise, researchers can develop the skills, knowledge, and competencies needed to plan, design, and execute clinical trials adapted to the local setting while adhering to the international ICH-GCP guidelines. In the long term, the implementation of this trial will help the establishment of a sustainable research network integrating EU and non-EU sites.

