### 2.2. Objectives and Endpoints

The study primary objective is to evaluate the safety of high-dose rifampicin (35 mg/kg/d) as part of a standard first line regimen using standard doses of isoniazid (5 mg/kg), pyrazinamide (25 mg/kg), and ethambutol (15–25 mg/kg) for 8 weeks in adult subjects with pulmonary or extrapulmonary DS-TB belonging to difficult to treat subgroups. The secondary objectives are to evaluate the tolerability, efficacy, bactericidal activity, pharmacokinetic/pharmacodynamics, and cost effectiveness of high dose rifampicin, among others. 

The primary safety endpoint is the proportion of participants and historical controls with one or more grade 3 or higher adverse events (AE) according to the CTCAE v5 or SAE at 8-weeks after treatment with high-dose rifampicin onset. Table 2 below describes in detail the analysis population and primary safety outcomes. The secondary tolerability endpoint includes the proportion of participants with any AE. The secondary efficacy endpoint includes the proportion of participants and historical controls who have sputum culture conversion at 8 weeks after treatment onset or a proportion of participants with clinical improvement according to the treating physician (if follow-up images are available for extra-pulmonary TB) but without a follow up sample at 8 weeks after treatment onset.

Most TB phase 2 trials complete their intervention at week 8 or earlier and then participant care is transferred to a public institution within the National TB programs, so the information about end of treatment and post-treatment outcomes is scarce [10,17,18]. In the RIAlta trial, after the intervention and the primary safety objective evaluation, an extended follow-up period will be offered to participants, in line with the phase 2b/c design suggested by Phillips et al. [19]. This will provide information about end-of-treatment outcomes and relapse incidence in the prospective group.

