### 2.9. Sample Size Assumptions and Justification

For the sample size calculation, a non-inferiority design is assumed and the upper limit of the 95% confidence interval (CI) of the difference of proportions in grade 3 or higher adverse events at 8 percentage points has been set. We assume that 5% of patients will not be assessable. Alpha risk is set in 0.1 and power in 0.8. Based on the previous literature and our previous experience, expected standard treatment grade ≥ 3 AE are 5–10% (mean 8%) among experimental arms and standard treatment arms. Considering this, the number of participants per arm has been calculated to be 134 participants. Because of the limited recruitment capacity for this trial, we could not target specific numbers of participants for each sub-group of risk factors. 

Based on a feasibility survey performed at the planning stage, the target enrollment rates per country were: Paraguay 6.25 participants per month; Spain, Portugal, and the Netherlands 1.6 participants per month.

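### Grade 3 or higher events are monitored prospectively in HR35ZE but read from routine records in controls, so under-recording in controls would inflate the adverse-event part of the primary difference

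*Protocol article*

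**What the plan says.** Section 2.2 defines one endpoint for both cohorts: "The primary safety endpoint is the proportion of participants and historical controls with one or more grade 3 or higher adverse events" by CTCAE v5, or a serious adverse event, at 8 weeks.

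The two cohorts supply it differently. For controls, section 2.5 describes a review of records from January 2017 to December 2019: "We will capture the severe or grade 3 adverse events and week 8 microbiological status". The Discussion adds: "This information will be likely available from historical controls although it was not systematically collected". For HR35ZE, the Discussion describes "adverse events monitoring and management guidelines, which will be harmonized at all centers for the prospective part".

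Section 2.8 gives two safeguards. One is standardized investigator training in assessing events. The other is Steering Committee review of grade 3 or higher and serious events in both cohorts to classify relatedness, with the Data and Safety Monitoring Board deciding where there is no consensus. The same section calls the regimen unsafe if the upper 95% limit of the difference exceeds 8 points.

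Section 2.10 widens the analysed outcome. It counts rifampicin-related grade 3 or higher events or SAEs, and also non-completion for other reasons and loss to follow-up.

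Section 2.9 plans on equal rates: "expected standard treatment grade ≥ 3 AE are 5–10% (mean 8%) among experimental arms and standard treatment arms". It makes no allowance for a difference in detection.

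**The concern.** The same endpoint is obtained by two procedures of different sensitivity. An event that a study team would notice and grade may be absent from a routine chart, and that control then counts as event-free. This matters most for findings that depend on someone looking. Some of the relevant events are laboratory findings: section 2.8 lists hyperuricemia among the most common adverse events, and section 2.4 refers to grade 3–4 hepatobiliary alterations.

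The article accepts that incomplete records hamper comparison of grade 1–2 events. For the primary endpoint it relies on the information being likely available. Neither safeguard in section 2.8 can recover an event that was never charted, and including all eligible patients (section 2.5) deals with selection, not detection.

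At stake is how a failed non-inferiority test can be read. It could reflect toxicity or closer surveillance, and the article describes nothing that would tell them apart.

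**Working it through.** **Inputs.** Margin: "difference of proportions in grade 3 or higher adverse events at 8 percentage points". Planning rate: 8% in both groups (section 2.9). Error rates: "Alpha risk is set in 0.1 and power in 0.8". Attrition: "We assume that 5% of patients will not be assessable". Assessable per group: 134 × 0.95 ≈ 127. Decision rule: upper 95% limit of the risk difference below 8 points (section 2.8). The control capture fraction *c* is not in the documents, so it is assumed and varied.

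**The plan's own figure.** With equal rates *p*, n = 2p(1−p)(z₁₋α + z₀.₈)² / 0.08².

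- p = 0.10, one-sided α = 0.10: 0.18 × (1.2816 + 0.8416)² / 0.0064 = 126.8, so 127; 127/0.95 gives 134. This reproduces the stated size.
- p = 0.08, same settings: 103.7, so 104; 104/0.95 gives 110.

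The stated size thus matches the top of the 5–10% range, not its stated mean. That is a separate matter; here it fixes n.

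**Effect of under-recording.** With true rate 8% in both groups, the observed control rate is 0.08c and the spurious excess is 0.08(1−c). The probability that the upper 95% limit falls below 8 points was obtained by exact binomial enumeration, with 127 per group and rates 0.08 and 0.08c:

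| Capture c | Observed control rate | Spurious excess (points) | Newcombe interval | Wald interval |
|---|---|---|---|---|
| 100% | 8.0% | 0 | 62% | 66% |
| 90% | 7.2% | 0.8 | 54% | 59% |
| 80% | 6.4% | 1.6 | 46% | 52% |
| 70% | 5.6% | 2.4 | 38% | 45% |
| 50% | 4.0% | 4.0 | 23% | 30% |

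**Check by normal approximation.** Power = Φ((0.08 − 0.08(1−c))/SE − 1.96). At c = 1, SE = √(2 × 0.08 × 0.92/127) = 0.0340 and power is 65%. At c = 0.5, SE = √((0.08 × 0.92 + 0.04 × 0.96)/127) = 0.0297 and power is 27%. Both agree with the table.

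**Separating out the alpha mismatch.** The 62–66% start is low partly because section 2.9 uses alpha 0.1 while the rule uses a 95% interval. With one-sided 0.10 in place of 1.96, the approximation gives 86%, 72% and 53% at 100%, 75% and 50% capture. The loss from under-recording remains.

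**The wider outcome of section 2.10.** Suppose half the control events are missed (8% against 4%) and 5% in each group count through non-completion or loss. The totals are 13% and 9%, a spurious +4 points. If controls have 2 more points of non-completion or loss, this drops to +2; with 4 more points it is 0; with 5 more it is −1. The sign depends on a quantity the documents do not give.

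**The case against.** The strongest reply has four parts.

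- **Direction.** A reader might infer that the bias always acts against HR35ZE. The documents do not support that. It holds for the adverse-event and SAE component alone. In section 2.10 non-completion and loss also count, may be more frequent in routine care, and can cancel or reverse the excess. A control whose record stops early might be classed as lost, hence unfavourable. This stands.
- **Size.** A reader might infer that the 8-point margin is used up. At an 8% rate that needs zero capture; the illustrated range takes 0.8 to 4.0 points. Nor does the article say that symptom-free laboratory events were never measured in controls, only that collection was not systematic. It gives no laboratory schedule for either cohort, and a common abstraction form may exist in the full protocol. The harmonized guidelines are introduced as an answer to the grade 1–2 gap. All of this limits the claim, but does not remove the contrast between prospective follow-up and chart review.
- **Disclosure.** Section 2.15 calls the design especially prone to bias and presents the results as informing future trials. That is fair, but it gives neither direction nor size and provides no analysis. Under-recording by itself does not produce a false claim of safety, but it can produce a false finding of harm.
- **Remedy.** Redefining the primary endpoint to drop laboratory findings without clinical action would remove some hepatotoxicity from the comparison and unsettle the 8% rate and the margin. This stands, so redefinition is not recommended.

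**Conclusion.** The concern holds for the adverse-event and SAE component. The article itself describes unequal ascertainment, and its safeguards do not reach unrecorded events. If charts capture 90% to 50% of control events, an equally safe regimen shows a spurious excess of 0.8 to 4.0 points, and its chance of meeting the rule falls from 62–66% to between 54–59% and 23–30%. These figures assume a true 8% rate in both groups, 127 assessable per group, 1:1 allocation (the abstract says at least 1:1), the 95% rule, and a capture fraction that no document supplies. They model adverse events alone.

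For the full outcome of section 2.10 the net direction is uncertain. The supportable conclusion is that a failed test could not be attributed to dose without further information on ascertainment. It is not that the comparison is necessarily biased against HR35ZE.

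**What to change.** Keep the primary endpoint and the 8-point margin, and add the following:

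1. Abstract events on one form in both cohorts, recording whether each was found on a protocol-scheduled or a clinically indicated test.
2. Tabulate on-treatment visits and laboratory tests by cohort.
3. Report the adverse-event and SAE component separately from non-completion and loss to follow-up.
4. Pre-specify three supportive analyses: (a) a comparison limited to events both sources can show, namely SAEs and symptomatic or clinically detected grade 3 or higher events; (b) a comparison limited to controls with a baseline and at least one on-treatment liver test, noting that such controls may have been tested because of symptoms; (c) a tipping-point analysis giving the control capture fraction at which the conclusion changes.
5. State that an unsafe result will be read alongside these.

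The cost is one extra field on the event form, counts of visits and tests from the control records, and some additional analysis. Sample size and decision rule are unchanged.
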